#### Process evaluation

The process evaluation will involve quantitative analysis of the psychological and engagement measures and qualitative analysis of interview transcripts relating to the acceptability of the intervention.

The extent of user engagement with Drink Less will be evaluated through descriptive statistics of the engagement measures. Detailed modelling of variations between participants will be conducted to explore variation in engagement and psychological measures by sociodemographic characteristics, baseline AUDIT scores and COVID‐19 measures (survey and national responses). A mediation analysis will be conducted to determine if any effect of group allocation on the primary outcome is mediated by changes in the psychological measures. The psychological measures will also be integrated into the modelling of effectiveness outcomes for Drink Less to identify links between the outcomes, participant engagement and psychological measures.

Anonymised interview transcripts on the intervention's acceptability will be analysed using a combined framework and thematic analysis approach. This involves initially coding participant responses according to the Theoretical Framework of Acceptability construct they are judged to represent best, then grouping similar responses within each construct inductively to generate content themes representing how that construct contributes to reported acceptability. Twenty‐six participants will be interviewed initially (13 from each group) [24], then data will be analysed and data collection will continue in an iterative process (adding 10 participants at a time) until thematic ‘meaning’ saturation is reached. Meaning saturation is defined as the point at which the issues are fully understood and no further dimensions, nuances or insights are found [62].

#### Health economic evaluation

The economic evaluation will take a two‐stage approach to analyse the cost‐utility of Drink Less from the NHS perspective. The first stage will be an analysis of the cost‐effectiveness of the app in the trial population over the duration of the trial itself (including follow‐up). Costs will include the cost of the interventions in both arms and the cost of NHS resource use (i.e. cost of changes in service use and treatments). The cost‐effectiveness analysis will take into account the total development cost of Drink Less but keep it separate from the incremental evaluation because there are no anticipated additional costs per user using the app. Effects will be measured in terms of (i) reduction in alcohol consumption and (ii) health‐related quality of life, measured in quality‐adjusted life years (QALYs). The cost‐utility will be measured in terms of Incremental Cost‐Effectiveness Ratio, the ratio between the difference in costs and difference in effects between the intervention and comparator groups.

As there can be a delay of several years between reductions in alcohol consumption and improvements in health [63], the full impacts of interventions designed to reduce alcohol consumption on health and healthcare costs may not be seen until well beyond the time horizon of an RCT. The second stage of the economic evaluation will address this limitation by using the established and widely‐used Sheffield Alcohol Policy Model [64, 65] to assess the longer‐term cost‐effectiveness of the intervention, if rolled out on a national level through active promotion to the public, over a 20‐year time horizon.

Both short‐ and long‐term evaluations will assess the impact on health inequalities using a Distribution Cost‐Effectiveness Analysis framework [66, 67]. Costs and QALY outcomes will be estimated separately by socioeconomic group, defined by social grade (AB, C1, C2, D or E). These group‐specific results will be combined with estimates of health pre‐intervention and the opportunity cost of additional healthcare spending to place the intervention on the ‘health equity impact plane’. Published estimates of inequality aversion, quantifying the extent to which society is willing to trade off changes in cost‐effectiveness for changes in health inequalities, will be used to identify the optimal strategy after accounting for the inequality impacts of each approach.

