**Figure 2 add15287-fig-0002:**
[figure not shown]
Flowchart of procedure

**Table 1 add15287-tbl-0001:** Schedule of enrolment and follow‐up assessments

Assessment	Time‐point			
	Baseline	1 month	3 months	6 months
Informed consent	x			
Eligibility screening	x			
Randomisation	x			
Intervention/comparator initiation	x			
Sociodemographic characteristics^a^	x			
Weekly alcohol consumption	x	x	x	x
AUDIT score and proportion of hazardous drinkers	x			x
Alcohol‐related problems or consequences and alcohol‐related injury				x
Use of healthcare services				x
Health‐related quality of life				x
Psychological measures	x			x
Engagement	x	x	x	x
Acceptability				x
Adverse events		x	x	x
Debriefing				x

^a^

Sociodemographic characteristics include: age, sex, ethnicity, education, occupation, income.

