#### Baseline assessment

Participants will complete a web‐based assessment of sociodemographic measures (see Measures) and their contact details (email address, telephone number and postal address) for follow‐up assessments.

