#### Follow‐up assessments

Follow‐up assessments will be conducted 1, 3 and 6 months after baseline. The 6‐month follow‐up assessment will assess the primary and secondary outcome measures and psychological measures; the follow‐up assessments at 1 and 3 months will assess the self‐reported weekly alcohol consumption only. Participants will have up to 30 days to complete each survey to maximise data retention. Participants will be sent up to three automated emails with a link to a web‐based survey for the follow‐up assessments on days 0, 5 and 9. Participants who do not complete the web‐based follow‐up assessment will be sequentially offered opportunities to do so via phone (called once per day on days 10–17), mailed survey (on day 18) and by postcard (on day 30). Participants will be compensated with gift vouchers of up to £36 for completing the three surveys: £6 for the survey at 1 and 3 months; £12 at 6 months with an additional £12 if the 6‐month survey is completed within 24 hours.

At the 6‐month follow‐up, participants will indicate whether they are happy to be called for a short interview about their experience of the trial; there is no additional compensation for this telephone interview. Acceptability will then be measured after the 6‐month follow‐up via telephone interviews.

Participants will be asked whether they experienced any unexpected consequences, adverse events or other harms from participating in the study (in an open‐ended question at the 1‐, 3‐ and 6‐month follow‐up) and whether they have used any other forms of support for alcohol reduction (at the 6‐month follow‐up).

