#### Secondary outcome measures

Change between baseline and 1‐ and 3‐month follow‐ups in self‐reported weekly alcohol consumption estimated over the last 1 and 2 months, respectively;Heavy episodic alcohol use (measured using AUDIT question 3) at 6‐month follow‐upProportion of hazardous drinkers (AUDIT score ≥8);Alcohol‐related problems or consequences and alcohol‐related injury (measured using the Alcohol Short Index of Problems) [43] at 6‐month follow‐up;Use of healthcare services (measured using the Service Use Questionnaire) [44, 45] at 6‐month follow‐up;Health‐related quality of life (measured using the EQ‐5D‐5L) at 6‐month follow‐up.

The self‐report AUDIT questionnaire has 10 items that measure alcohol consumption, harms and dependence. The AUDIT is a reliable and standardised alcohol‐related outcome measure that is commonly used in alcohol trials [5, 23]. It has a high test–retest reliability when completed online [46], allows the derivation of a core outcome set for consistency across trials and minimises research waste and selective reporting [47]. The timeframe of the AUDIT will be modified to refer to the past 6 months when asked at the 6‐month follow‐up so this can be directly compared with the baseline AUDIT, which will also refer to the past 6 months. The extended AUDIT‐C when asked at the 1‐ and 3‐month follow‐up will refer to the past 1 month and 2 months, respectively, to capture participants’ alcohol consumption since the last survey.

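### EQ-5D-5L and service use are collected at 6 months only, so within-trial QALYs rest on unstated baseline and path assumptions and neither QALYs nor costs can be adjusted for their own baseline

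*Protocol article*

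**What the plan says.** Timing of the two economic instruments, all in the protocol article:

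- Secondary outcome measures lists "Health‐related quality of life (measured using the EQ‐5D‐5L) at 6‐month follow‐up". The entry "Use of healthcare services (measured using the Service Use Questionnaire" carries the same 6-month timing.
- Table 1 ("Schedule of enrolment and follow‐up assessments") has a row "Use of healthcare services" and a row for health-related quality of life. Each has one mark, in the 6-month column. The rows for AUDIT score and for psychological measures are marked at both baseline and 6 months.
- Follow-up assessments states that "the follow‐up assessments at 1 and 3 months will assess the self‐reported weekly alcohol consumption only".
- Baseline assessment says "Participants will complete a web‐based assessment of sociodemographic measures (see Measures) and their contact details"; it names neither instrument.

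The section Health economic evaluation plans a first-stage analysis in the trial population from baseline through follow-up. Effects are reduction in alcohol consumption and QALYs. Costs are those of the interventions and of NHS resource use, the latter glossed as "i.e. cost of changes in service use and treatments". The cost-effectiveness ratio is defined on differences between the two arms. For the inequality analysis, "Costs and QALY outcomes will be estimated separately by socioeconomic group", with the grades AB, C1, C2, D and E, and these results are combined with estimates of pre-intervention health whose source is not given. The section states no assumption about baseline utility or its course over the 6 months.

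**The concern.** A QALY is utility accumulated over time. With one utility value per person, at the end, the area under that person's utility curve is not defined until a starting value and a path are assumed. The schedule gives neither, and the economic section does not say what will be assumed.

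Two things are lost. First, change within a person cannot be measured for utility or for service use. Second, neither outcome can be adjusted for its own baseline. Such adjustment would sharpen the comparison and correct for arms that happen to start apart. The second loss weighs most where strata are small, and the plan does estimate results by social grade. A participant who is lost before 6 months also contributes no utility or service-use value at all.

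Short-horizon cost-utility is one of the article's research questions, and cost-effectiveness is part of the trial's stated aim. An analysis plan can choose a model later, but it cannot recover a pre-randomisation measurement that was never taken.

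**Working it through.** There is no figure in the article to reproduce on this point. The check sets the schedule against the economic plan and then sizes the consequences.

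**Inputs from the article.** Horizon T = 0.5 year (baseline to 6 months); 2781 per arm, 1:1 allocation (Sample size); both instruments at 6 months only.

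**Inputs assumed (not in the article).** Utility SD 0.15 to 0.25; correlation between baseline and 6-month utility 0.5 to 0.8; one social grade holding 5% of each arm; an illustrative 6-month utility difference of 0.01. Complete follow-up is taken for simplicity.

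**1. What one utility value leaves open.** Let b be the difference between arms in baseline utility and d the difference at 6 months.

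- Linear change: incremental QALY = T × (b + d)/2 = 0.25(b + d). With b set to 0 this is 0.25d.
- Immediate step, with b = 0: T × d = 0.50d.
- Difference arising only in the last month: d/12, about 0.083d.

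For d = 0.01 these give 0.0025, 0.0050 and 0.0008 QALY. The same observed difference thus gives a twofold range between linear and step change, and a sixfold range between step and last-month change. The common starting level cancels between arms, but b = 0 has to be assumed because it is not observed.

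**2. How large b can be by chance.** SE(b) = SD × √(2/2781).

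- SD 0.15: 0.0040. SD 0.20: 0.0054. SD 0.25: 0.0067.
- Times T/2 = 0.25, this is 0.0010 to 0.0017 QALY.

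In a grade with 5% of each arm, n = 0.05 × 2781 ≈ 139. With SD 0.20, SE(b) = 0.20 × √(2/139) ≈ 0.024, about 4.5 times the whole-trial value of 0.0054 (√20 ≈ 4.5).

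**3. What own-baseline adjustment would gain.** Adjustment multiplies the variance of the 6-month utility difference by 1 − ρ².

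| ρ (assumed) | 1 − ρ² | variance reduction | SE of 0.25d, SD 0.20 |
|---|---|---|---|
| none | 1 | 0% | 0.00134 |
| 0.5 | 0.75 | 25% | 0.00116 |
| 0.7 | 0.51 | 49% | 0.00096 |
| 0.8 | 0.36 | 64% | 0.00080 |

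**4. What a baseline value does not settle.** The range in step 1 comes from the unobserved path between 0 and 6 months. With b known, linear and step change still give different answers. A baseline EQ-5D-5L therefore addresses steps 2 and 3 but not the path.

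**The case against.** A reader might infer that QALYs and costs cannot be computed at all under this schedule. The article does not support that. Its cost-effectiveness ratio needs only differences between arms. Randomisation makes expected baseline utility and service use equal, so an incremental QALY follows from 6-month utilities once a path is declared. Incremental cost follows from one retrospective questionnaire if its recall period, which the article does not give, covers follow-up. The article promises neither an area-under-the-curve method nor baseline adjustment, so their absence contradicts nothing it states. This stands.

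Three further stronger readings also fail:

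- The gloss on cost could be taken to require change within a person from an unmeasured baseline. It sits in a passage about incremental differences and can equally mean a difference between arms.
- Social grades might be thought to bias the inequality analysis because they start at different utility levels. Incremental results are contrasts between arms within a grade, so such differences cancel in expectation. The real weakness there is chance imbalance in small strata.
- The twofold range in QALYs might be blamed on the missing baseline. It comes from the path.

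It can also be said that the article's lists are not exhaustive: Table 1 omits the COVID-19 survey, and the baseline section omits the psychological measures. That does not help here, because two places put both instruments explicitly at 6 months. Finally, the article treats response burden as critical in digital trials when it justifies its short primary measure, and it relies on a 20-year model because health gains may come late. Both lower the weight of the point. Neither supplies the missing precision or states the assumptions.

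**Conclusion.** The point holds as a design limitation of the economic evaluation. With both instruments at 6 months only, the within-trial QALYs depend on an unstated assumption of equal baseline utility and an unstated utility path; change within a person cannot be measured; and neither QALYs nor costs can be adjusted for their own baseline.

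The loss of precision corresponds to a forgone variance reduction of 25% to 64% for the 6-month utility difference, if the correlation is 0.5 to 0.8. That range is an assumption, as are the utility SDs and the 5% stratum used above. Chance imbalance stays uncorrectable, most of all in small social-grade strata. Separately, the incremental QALY is 0.25d or 0.50d according to whether linear or immediate-step change is assumed, and a baseline measurement alone would not narrow that.

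The analysis remains feasible. The primary outcome and the effectiveness conclusion are untouched. This is a cheap improvement worth making, not one on which the trial's validity depends.

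**What to change.** 1. Add the EQ-5D-5L and the Service Use Questionnaire to the online baseline assessment, before randomisation, and update Table 1 and the list of secondary outcomes to match.
2. Regress QALYs and costs on arm, with baseline utility and baseline cost as covariates, overall and within social grade.
3. Declare the assumed utility path between baseline and 6 months, and report the incremental QALY under both linear change (0.25d when baselines are equal) and immediate-step change (0.50d).
4. For anyone already randomised without baseline values, state that equal baseline utility and service use are assumed.

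The cost is a few extra minutes in an online form. Any additional drop-out would occur before randomisation and so could not bias the comparison between arms, though it could slow recruitment slightly. Items 3 and 4 need only text.

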### Ethical approval

Ethical approval has been obtained from UCL Research Ethics Committee (16799/001).

### Dissemination policy

Results will be disseminated by open‐access peer‐reviewed journal articles, presentations at scientific conferences, press releases, a stakeholder workshop and blog posts. NIHR authorship guidelines will be followed. Study materials, anonymised data and code will be made available on Open Science Framework (on the project page: https://osf.io/q8mua), and the source code for the app will be released under the GNU General Public License (v3) on GitHub.

## Discussion

This study will provide evidence on the effectiveness and cost‐effectiveness of the Drink Less app—a theory‐ and evidence‐informed intervention—for the reduction of hazardous and harmful alcohol consumption. The embedded mixed‐methods process evaluation will evaluate the extent of user engagement with Drink Less and whether user engagement moderates or changes in psychological measures mediate the effectiveness of the intervention and participants’ views on the acceptability of the intervention. Furthermore, the use of behavioural science in the development and refinement of the Drink Less app and the trial methodology will improve the understanding of what works for whom and why. Drink Less collects detailed user engagement and behavioural data of potential value in advancing its underpinning theory [68], which can inform future behaviour change interventions. The principles of Open Science will continue to be followed, which is important for efficient scientific progress.

Drink Less is in a good position for future implementation in healthcare settings because it is already aligned with the criteria from the NHS Digital Assessment Questionnaire and with the NICE Evidence for Effectiveness Framework and Code of Conduct for Digital Health [69, 70, 71]. The app will be submitted to the NHS Apps Library if found to be effective, which may result in healthcare practitioners recommending or prescribing the app to patients [72]. Drink Less is a standalone app and therefore, in a strong position to be actively promoted on a national level, through media contacts and relevant organisations, to encourage use of the app amongst wider society. A sustainability model will be developed as part of this research project to maximise the impact of the app by enabling long‐term planning for its implementation, adoption and future development and will inform the long‐term economic analysis in terms of potential reach and costs. A current limitation is that Drink Less is only available on iOS devices though this RCT will provide a proof of concept and strong rationale, if effective, for developing a native Android version, which would maximise the potential impact of Drink Less on public health. A potential limitation of the trial is the choice of the NHS website as the comparator instead of an app‐based intervention that would allow us to directly compare the recommendation to download one of two apps. However, using the NHS website as the comparator condition is of direct policy relevance and strengthens the public health impact of the study.

There are two main anticipated challenges with this trial: recruitment and retention rates that we have attempted to minimise as follows. A multi‐pronged recruitment strategy is planned, including placing an advert on a NHS webpage, which provides the ability to access a large number of drinkers. A higher rate of recruitment than is currently required (265 participants per month) was achieved in the factorial trial of Drink Less (355 per month) [13] with web‐based recruitment and screening. However, a contingency plan is in place that involves advertisements placed on Google and Facebook (following the methods used in a similar trial [73]) and use of a recruitment company. We will also calculate Bayes factors, which in the situation of under recruitment will allow us to distinguish between two interpretations of a non‐significant result: (i) support for the null hypothesis of ‘no effect’ and (ii) data are insensitive to detect an effect [74, 75]. To maximise the overall retention rate, financial incentives will be offered as a reasonable acknowledgement of participants' time, and a range of methods will be used for follow‐up contact sequentially, which has been shown to improve response rates [76]. The trial cost per participant and methods of follow‐up contact are comparable with similar studies that achieved high retention rates [73, 77]. The intention‐to‐treat approach to analysis is conservative, meaning that if a follow‐up rate similar to that in other trials is achieved, then if anything the effect size will be an underestimate.

We acknowledge that the research team is evaluating an app that it has developed and that there may be a perceived bias. The team have no financial stake in the app and the code is available in Github by the GNU General Public License (v3). The trial has been designed to meet the Cochrane Risk of Bias criterion of ‘low risk’ and we have followed best practice guidelines to ensure a robust evaluation is conducted, including blinding and oversight by independent trial steering and data monitoring committees. The data will be analysed in accordance with a pre‐specified analysis plan approved by the committees and uploaded onto Open Science Framework before the start of data analysis.

## Conclusions

This study will be the first RCT of an alcohol reduction app for the general population in the United Kingdom, thereby starting to build a strong evidence base on the effectiveness and cost‐effectiveness of health‐related apps. The RCT will be able to directly inform the pragmatic question of interest: whether it is worth investing resources into promoting the Drink Less app.

## Clinical trial registration

ISRCTN64052601.

## Ethics committee approval

16799/001.
